### Publication of the trial results

The trial results will be published by the members of the Steering Committee, on behalf of the investigators.

## Discussion

We present the protocol of a randomised clinical trial designed to test the safety and feasibility of vertebral artery stenting in patients with a symptomatic stenosis ≥ 50% of a vertebral artery. Case reports suggest that vertebral artery stenting is relatively safe with a periprocedural risk of stroke or death ranging from 1.6 to 13.8%.

In a recent review, stenting of the extracranial vertebral artery in 313 patients resulted in technical success in 98 to 100% of the cases, with a 0.3% risk of death and 5.5% risk of neurological complications [7]. Stenting of the distal (intracranial) vertebral artery in 283 patients was associated with technical success in 97 to 98%, but with higher complication rates: a case fatality rate of 3.2% and a 17.3% risk of neurologic complications. The differences in complication rates of stenting between the proximal and distal vertebral artery may be explained by the fact that stenting of the distal vertebral artery was more frequently performed in the acute phase of vertebral or basilar occlusion and was considered technically more difficult.

The interpretation of outcome after vertebral stenting is complicated by the lack of data on the risk of recurrent stroke in patients with vertebral stenosis on best medical therapy alone. To date no reliable data are available on the prognosis of VB stroke. In a recent review, the risk on recurrent stroke in the acute phase (up to seven days) is considered probably higher in patients presenting with a VB event compared with patients presenting with carotid events [1].

Stenting of the proximal vertebral artery might be associated with a relatively high rate of restenosis at follow-up. In the above-mentioned review, restenosis of the proximal vertebral artery has been reported in a quarter of the cases after a mean follow-up of 11.8 months [7]. The definition of restenosis varied for the different studies. Detection criteria included maximal flow velocity in the stenosis in relation to prestenotic or poststenotic segments, pulsatility, anterograde or retrograde direction of flow, and the presence of end-diastolic flow signal proximal to the lesion on duplex ultrasound. Restenosis in the distal vertebral artery was detected in about one fifth of the cases after a mean follow-up of 7.5 months. Most of the patients with restenosis remained asymptomatic. It has been suggested that neointimal proliferation following stent placement has a lower risk on thromboembolic events than atherosclerosis [17]. Possible predictors for restenosis are high age, low pre-treatment vessel diameter and post-treatment stenosis [7,18,19].

Since the natural course of a symptomatic vertebral artery stenosis in patients on best medical treatment alone is unknown and the exact indications for vertebral stenting are unclear a randomised clinical trial is needed. By comparing outcome in patients on best medical treatment alone and patients with vertebral artery stenting, a conclusion can be drawn on the safety and feasibility of vertebral artery stenting in symptomatic vertebral artery stenosis.

Conventional angiography is the gold standard for the diagnosis of vertebral artery stenosis. Randomisation to either stenting or best medical treatment in this study will take place before angiography is performed. It is not considered ethical to perform conventional angiography in each patient included in the study because this procedure is associated with a small but inevitable risk of stroke. This might lead to randomisation of patients to stenting without a significant stenosis on conventional angiography. In approximately half of the patients (patients randomised to best medical treatment alone), grading of the stenosis will be done on the basis of CTA or MRA and duplex ultrasound alone. Studies of sufficient quality validating the accuracy of diagnosing and grading vertebral artery stenosis with non-invasive imaging techniques against the gold standard of intra-arterial angiography are scarce. No studies have compared the different imaging modalities against intra-arterial angiography in the same cohort of patients. Contrast-enhanced MRA and possibly CTA may be more sensitive in diagnosing vertebral artery stenosis than duplex ultrasound [20].

The trial has started 1 June 2008 in two centres in the Netherlands. Four other Dutch centres are expected to join the trial shortly. Other centres, also from other countries than the Netherlands, that have adequate experience with the management of vertebral artery stenting are welcome to participate.

### Trial Coordination Centre

The Trial Co-ordination Centre is located at the Trial Office Neurology of the Department of Neurology of the University Medical Centre, Utrecht, The Netherlands. The centre will be staffed by the trial co-ordinator and a data manager.

### Data Monitoring and Safety Committee

The DMSC performs analyses of the unblinded data on a permanent basis and formulates recommendations for the Steering Committee on the continuation of the trial. The Data Monitoring Committee may also offer unsolicited recommendations.

Members of the Data Monitoring Committee are being sought.

## Appendix. definitions of vascular complications

1. Death from vascular causes:

a. Fatal cerebral infarction: cerebral infarction causing an increase of handicap to Rankin 4 or 5, followed by death. Death should have been an unlikely event without the preceding infarction.

b. Fatal cerebral hemorrhage: cerebral haemorrhage causing an increase of handicap to Rankin 4 or 5, followed by death. Death should have been an unlikely event without the preceding bleeding.

c. Fatal myocardial infarction: Documented myocardial infarction (see 6) followed by death, at least one hour after onset of symptoms.

d. Definite sudden death: witnessed sudden death with reliable observation of timing; i.e. patient died within one hour after onset of symptoms.

e. Probable sudden death: witnessed death, but unreliable data on timing of events, or found dead and previously "healthy."

f. Terminal heart failure.

g. Fatal arterial bleeding.

h. Other fatal vascular complication, e.g. gastric bleeding, pulmonary embolism.

2. Cerebral infarction.

a. Definite new cerebral infarction: clinical evidence of the sudden onset of a new neurological deficit, persisting for more than 24 hours, with a corresponding new infarct on a repeat CT scan.

b. Probable new cerebral infarction: clinical evidence of the sudden onset of a new neurological deficit, or an increase in an existing deficit, persisting for more than 24 hours, without a new infarct on repeat CT scan.

3. Intracerebral haemorrhage

a. Clinical evidence of a sudden new neurological deficit, or an increase in an existing deficit, persisting for more than 24 hours, with a corresponding cerebral haemorrhage on a CT or MRI scan.

4. Subarachnoid haemorrhage

a. A sudden unusual headache and/or a reduction in consciousness with a corresponding subarachnoid haemorrhage on CT or MRI, or signs of subarachnoid haemorrhage in the cerebrospinal fluid.

5. Unspecified stroke

a. Clinical evidence of a sudden new neurological deficit, or an increase in an existing deficit, persisting for more than 24 hours, with no imaging performed.

6. Myocardial infarction

a. Myocardial infarction: At least two of the following characteristics have to be documented: a history of chest discomfort for at least half an hour, specific cardiac enzymes more than twice the upper limit of normal, or the development of specific abnormalities (e.g. Q waves) on the standard 12-lead electrocardiogram.

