### Outcome assessment

Clinical outcome assessment will be performed by three independent adjudicators on the basis of an anonymised written description of the outcome event and ancillary investigations. This description will be made by the research physician in such a way that the adjudicators will remain masked to the allocated treatment.

The primary outcome measure will be vascular death, non-fatal myocardial infarction, or non-fatal stroke (neurological deficit lasting longer than 24 hours for which no other cause than a stroke can be found) within 30 days after start of the treatment (see Appendix for definitions).

Secondary outcome measures will be vascular death, non-fatal myocardial infarction, or non-fatal stroke during follow-up. Other outcome measures include any stroke in the supply territory of the symptomatic vertebral artery during follow-up and the degree of stenosis of the symptomatic vertebral artery after one year, as assessed with both Duplex ultrasound and CT angiography.

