### Data collection

At baseline, medical history (including clinical signs and symptoms, duration of the neurological deficit, number of attacks, previous cardiovascular events, previous cardiovascular treatments, vascular risk factors, and medication) will be assessed and clinical and neurological examination (including blood pressure) will be carried out. The baseline neurological and functional status will be assessed with the National Institutes of Health Stroke Scale (NIHSS) and with the modified Rankin Scale [10,13]. The vascular risk factors (hypertension, smoking, diabetes, lipid disorders) will be noted. Laboratory investigations will include complete blood count, erythrocyte sedimentation rate, C-reactive protein, and cholesterol.

The degree of stenosis in the vertebral artery will be assessed with duplex ultrasound and MRA, CTA, or conventional angiography. Except for duplex ultrasound, the degree of the stenosis will be calculated by dividing the residual lumen (N) by vessel diameter at a point distal to the stenosis where the normal vessel calibre has been restored (D), and applying the formula: (1 - N/D) × 100% = degree of stenosis [14]. To assess the location of stenosis, the vertebral artery is divided into four sections: V1-V3 form the extracranial vertebral artery and V4 forms the intracranial vertebral artery [15]. The type of plaque in the vertebral artery and the presence and degree of stenosis in other brain feeding arteries will be noted.

CT and MRI scans will be performed to investigate the presence and type of a cerebral infarct (supply territory of intracerebral artery, small vessel disease, large vessel disease)

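### Appendix item 2 does not match the main-text stroke definition: worsening with a CT-proven infarct fits no item, and an infarct imaged by MRI alone is not clearly placed

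*Protocol article*

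**What the plan says.** Outcome assessment defines the stroke component of the primary outcome clinically, as a "neurological deficit lasting longer than 24 hours for which no other cause than a stroke can be found". It sets no imaging condition and does not separate a new deficit from a worsened one. The same sentence then sends the reader elsewhere: "within 30 days after start of the treatment (see Appendix for definitions".

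Three Appendix items matter for a suspected infarct:

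- **Item 2a (definite infarction):** "sudden onset of a new neurological deficit, persisting for more than 24 hours, with a corresponding new infarct on a repeat CT scan".
- **Item 2b (probable infarction):** "clinical evidence of the sudden onset of a new neurological deficit, or an increase in an existing deficit, persisting for more than 24 hours", and "without a new infarct on repeat CT scan".
- **Item 5 (unspecified stroke):** a new or worsened deficit "persisting for more than 24 hours, with no imaging performed".

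Two neighbouring items are useful for comparison. Item 3 (intracerebral haemorrhage) accepts a worsened deficit and either CT or MRI. Item 4 (subarachnoid haemorrhage) also accepts either modality.

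Data collection states that "CT and MRI scans will be performed to investigate the presence and type of a cerebral infarct". That section opens with baseline assessments and does not say which modality is used for outcome events.

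**The concern.** Of the items that rest on a neurological deficit (2a, 2b, 3 and 5), only 2a leaves out worsening of a deficit already present. Item 2 is also the only imaging-based stroke item that names CT alone. Both look like drafting slips, but they sit in the text to which the primary outcome refers for its definitions.

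The affected presentation is foreseeable. Enrolment criteria admit patients after a TIA or non-disabling stroke with a modified Rankin score up to 3. Some will carry a residual deficit, and a recurrence may show as worsening of it.

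Three masked adjudicators judge events from written descriptions. Where the clinical definition and the Appendix give different answers, no rule says which prevails, and adjudicators may resolve the conflict differently. The same stroke component also enters the secondary outcome during follow-up. Under Statistical considerations, the resulting event rates are meant to size a later definitive trial.

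**Working it through.** **Step 1: cross deficit type with imaging.** Assume a deficit lasting more than 24 hours, ischaemic and with no other cause found. The cells show which of items 2a, 2b and 5 apply.

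| Imaging of the event | New deficit | Worsened existing deficit |
|---|---|---|
| None | 5 | 5 |
| CT shows new infarct | 2a | **none** |
| CT negative, no MRI | 2b | 2b |
| CT negative, MRI shows infarct | 2b | 2b |
| MRI shows infarct, no CT | unclear | unclear |
| MRI negative, no CT | unclear | unclear |

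- *Worsened deficit, new infarct on CT.* 2a fails because the deficit is not new, 2b because CT is positive, and 5 because imaging was done. The condition that shuts out 2b is this: "or an increase in an existing deficit, persisting for more than 24 hours, without a new infarct on repeat CT scan". The same patient with a negative CT would be a probable infarction, so stronger evidence removes the category.
- *CT negative, MRI positive.* This meets 2b. It is a stroke, but labelled only probable despite the imaging proof.
- *MRI without repeat CT.* 2a fails for lack of a CT and 5 because imaging was done. 2b applies only if the absence of a CT infarct is read to include the case where no CT was made.

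**Step 2: compare with the main text.** Under the clinical definition in Outcome assessment, all twelve cells count as stroke. The two texts therefore disagree outright in one cell and may disagree in four.

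**Step 3: reproduce the planned figures.** These come from Statistical considerations.

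- Stenting arm, 7 events in 90: 7/90 = 7.8%. The exact binomial limits are the 0.025 quantile of Beta(7, 84) and the 0.975 quantile of Beta(8, 83), which are 3.18% and 15.37%. The article states 3.2 to 15.4%.
- Medical arm: 90 × (1 + 4)/2 = 225 patient-years, and 7% × 225 = 15.75, taken as 16 events. The exact Poisson limits are 4.06% and 11.55% per year. The article states 4.1 to 11.5%.

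Both intervals are reproduced. The definitional mismatch makes neither of them wrong.

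**Step 4: scale only.** One event is 1/90 = 1.1 percentage points, or 1/7 = 14% of the planned seven. The number left uncounted is an assumption, shown from 0 to 2:

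| Events left out (assumed) | Rate | 95% CI |
|---|---|---|
| 0 | 7/90 = 7.8% | 3.2 to 15.4% |
| 1 | 6/90 = 6.7% | 2.5 to 13.9% |
| 2 | 5/90 = 5.6% | 1.8 to 12.5% |

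The seven are not seven strokes, since the primary outcome also includes vascular death and myocardial infarction. The table shows what one event is worth; it does not forecast any loss.

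**The case against.** The strongest reply is that the main text already settles the matter. Its clinical definition captures every case above, and nothing says that the Appendix overrides it. To reject a CT-proven infarct with clinical worsening, adjudicators would have to set that definition aside and discard better evidence than 2b accepts. On this view only the definite or probable label is in doubt, and the composite is unchanged.

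Much of this stands, and it rules out three stronger readings.

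- A reader might infer that true strokes fit no definition and will be lost. The documents do not support that, because the main-text definition covers them.
- A reader might infer that every infarct seen only on MRI is excluded. With a negative repeat CT it falls under 2b and counts. The gap is confined to events with no repeat CT, and even there it depends on how 2b is read. The article does not show that a work-up without CT would be usual: the Data collection sentence stands among baseline assessments, and the imaging that Follow-up specifies after an ischaemic stroke is duplex and CT angiography of the artery.
- A reader might infer a bias of one or two events in seven. The documents give no share of recurrences that present as worsening, and the Rankin criterion is only an upper limit.

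The reply fails on one point. The main text does not stand alone, because it refers to the Appendix for the definitions of this outcome. Two operative texts that differ on a foreseeable event, with no order of precedence, are a defect even if sensible adjudicators would probably resolve it well. Nor is this condensation by the article: the criteria are written out in full, and the fault lies in what they say.

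**Conclusion.** The point holds as a mismatch between two operative definitions of a primary-outcome component. One cell is a definite gap: a worsened deficit with a new CT infarct meets none of items 2a, 2b and 5. The cells with MRI and no repeat CT are ambiguous, and an infarct seen on MRI after a negative CT is counted but under-labelled.

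Loss of events is possible, not certain, and no stated interval or sample size is wrong. The effect can be sized only per event, at 1.1 percentage points in the stenting arm. It arises only if an adjudicator applies the Appendix literally and gives it precedence over the main text. The correction is worth making because planned event numbers are small and it costs almost nothing.

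**What to change.** 1. In item 2a, add worsening of an existing deficit beside a new deficit, as items 2b, 3 and 5 already do, and accept a corresponding new infarct on repeat CT or MRI.
2. In item 2b, keep the clinical wording and make the imaging condition no new infarct on repeat CT or MRI. Make clear that this means none on whichever modality was used, so that a negative CT with a positive MRI moves to 2a.
3. State under Outcome assessment that any event meeting the clinical definition there counts as stroke, and that the Appendix items only assign the subtype.

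One check when adding the third statement: item 4 can be met by headache or reduced consciousness without a deficit lasting 24 hours. The sentence should say whether such a haemorrhage counts, so that the repair does not open a mismatch in the other direction.

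The cost is two wording changes and one added sentence, carried into the adjudication form. No new imaging, visit or analysis is needed. Any events already adjudicated should be checked against the new wording.
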